**Figure 1 F1:**
[figure not shown]
Study flow chart participant time line. HSCT, haematopoietic cell transplantation; IMT, intestinal microbiota transplant.

### Data collection and management

#### General approach

Case report forms (CRFs) for the study will be in English, using generic names for concomitant medications wherever possible. All written material to be used by participants must use vocabulary that is clearly understood and be in the language appropriate for the study site. The electronic CRF (eCRF) database will be in OpenClinica. The investigator (or delegated member of the site study team) will record all data relating to protocol assessments and procedures, laboratory, safety and efficacy data in the eCRF. All trial documentation, including that held at participating sites and the trial coordinating centre, will be archived for a minimum of 20 years following the end of the study.

#### Confidentiality

The investigator will ensure that the participant’s confidentiality is maintained. On the CRF or other documents submitted to the sponsors, participants will be identified by a participant ID number only. Documents that are not submitted to the Sponsor (eg, signed informed consent form) should be kept in a strictly confidential file by the investigator. The investigator shall permit direct access to participants’ records and source documents for the purposes of monitoring, auditing, or inspection by the sponsor, authorised representatives of the sponsor, NHS (National Health Service), Regulatory Authorities and RECs.

The investigators and study site staff will comply with the requirements of the Data Protection Act 2018 concerning the collection, storage, processing and disclosure of personal information and will uphold the Act’s core principles.

#### Oversight and monitoring

A trial steering committee (TSC) will be convened, including as a minimum an independent chair, independent clinician, the chief investigator, independent statistician, trial manager and PPI representative. The role of the TSC is to provide overall supervision of trial conduct and progress. A trial management group (TMG) will also be convened, including the chief investigator, coinvestigators and key collaborators, trial statistician and trial manager. The TMG will be responsible for the day-to-day conduct of the trial and operational issues. Furthermore, an independent data monitoring committee (IDMC) will be convened to include as a minimum an independent oncologist chair, an independent oncologist and an independent statistician. The role of the IDMC is advisory to the TSC, to ensure the highest standard of patient safety and data integrity.

The IDMC may consider recommending the discontinuation of the trial if the recruitment rate or data quality are unacceptable, or if any issues are identified that may compromise patient safety. In the case of early discontinuation of the study, response assessments will be completed for each participant, as far as possible.

The study will be monitored periodically by trial monitors to assess the progress of the study, verify adherence to the protocol, International Conference on Harmonisation for Good Clinical Practice (ICH GCP) E6 guidelines and other national/international requirements and to review the completeness, accuracy and consistency of the data. Monitoring will be conducted centrally/remotely from the coordination centre and on-site. Monitoring procedures and requirements will be documented in a monitoring plan, developed in accordance with the risk assessment.

Quality control will be performed according to ICTU internal procedures. The study may be audited by a quality assurance representative of the sponsor and/or ICTU. All necessary data and documents will be made available for inspection.

The study may be a participant to inspection and audit by regulatory bodies to ensure adherence to GCP and the NHS Research Governance Framework for Health and Social Care (second Edition).

### Statistical considerations

#### Sample size and powering

Currently published data on alpha diversity change in patients undergoing HCT and/or IMT span different study types, vary in quality/granularity, and use different alpha diversity indices. The evidence available suggests larger decreases in alpha diversity at approximately 1-month post-HCT compared with baseline in patients who do not receive IMT relative to those that do.^2 6 8 18 19^ Fitting a mixed-effects model (with fixed effects for arm, time (day), their corresponding interaction and a random per-patient intercept effect) with quadratic splines at 5 df (3 internal knots) to longitudinal change in alpha diversity data (measured with inverse Simpson’s index) from baseline,^2^ IMT patients had an expected change in baseline alpha diversity at day 28 post-HCT 3.46 (pooled SE=2.19) units more than placebo (IMT mean change=−4.70, SE=1.44, n=14; placebo mean change=−8.16, SE=1.66, n=11). We have used these results on IMT post-HCT to design our study of IMT pre-HCT versus placebo.

Our null hypothesis is there is no difference between the change in days 28±3 days alpha diversity (inverse Simpson’s) post-HCT from baseline in patients receiving pre-HCT IMT compared with patients receiving placebo capsules (ie, the difference in between-arm changes from baseline is zero). Using a two-sample t-test to compare IMT-arm change to placebo-arm change with two-sided alpha controlled at 20%,^20 21^ we need 46 patients randomised 1:1 between IMT and placebo (23 per arm) to have ≥80% power to detect a between-arm difference of 3.46 units (with pooled SD of 5.45 estimated at day 28 post-HCT from mixed-effects model). To account for dropouts at a rate of up to 8% across both arms, we will recruit 50 patients in total. Modelling and sample size calculations have been performed using R V.3.6.1.

#### Statistical analysis

##### Overall approach

Statistical analyses will be formally documented within a detailed statistical analysis plan (SAP) and structured using the estimand framework (as described in the ICH E9 (R1) addendum on estimands and sensitivity analysis in clinical trials^21 22^ with intercurrent events and subsequent analysis strategies defined accordingly. Protocol non-adherence and other non-defined intercurrent events will be incorporated into analysis via a treatment policy where the patient is assessed based on their randomised arm regardless of the event in question. Any deviations from the SAP will be documented and signed off by the statisticians and CI and filed in the Trial Master File.

##### Primary estimand

Population: Adults with ALL, AML, AL of ambiguous lineage, high-risk MDS, CMML, and CML in blast phase, considered suitable/fit for allogeneic HCT.

Treatment: Capsulised IMT versus matched capsulised placebo.

Variable: Stool microbiota diversity post-HCT is defined as the change in alpha diversity (measured as inverse Simpson’s index) between IMT administration(at 14±3 days prior to HCT) and 28±3 days after HCT.

Population-level summary: The model-produced estimate for the treatment×time interaction effect at day 28.

Intercurrent events: Death, adverse/serious adverse events (AEs/SAEs), rescue therapy outside of antibiotic use, loss to follow-up/withdrawal.

Strategy to handle intercurrent events: Treatment policy will be used to handle patient all defined intercurrent events, any patient response-assessment data collected postrandomisation will still be used in the analysis model if day 28 data is unavailable.

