##### Secondary estimands

(1) Assessment of tolerability and acceptability of treatment versus placebo through the Functional Assessment of Cancer Therapy measured using health-related quality of life and patient perspective questionnaires.

Population: As per primary estimand.

Treatment: As per primary estimand.

Variable: Scores arising from health-related quality of life EQ-5D-5L (EuroQol-5 descriptive-5 level) and EORTC patient perspective (EORTC_QLQ-C30) questionnaires.

Population-level summary: The model-produced estimate for the treatment×time interaction effect at day 28, plus at follow-up time points days 100, day 200 and day 365.

Intercurrent events: Death, AE/SAEs, rescue therapy outside of antibiotic use, loss to follow-up/withdrawal.

Strategy to handle intercurrent events: Treatment policy as primary estimand

(2) Assessment of changes in inverse Simpson’s index and other measures of gut microbiome diversity across all time points assessed, including alpha diversity and richness (ie, as measured via Chao-1, Shannon, Faith’s PD) and beta-diversity (Aitchinson’s distance) as well as changes in gut microbiome taxonomic composition.

Population: As per primary estimand.

Variable(s): As per primary, plus Chao-1, Shannon, Faith’s PD, Aitchinson’s distance and taxonomic composition.

Population-level summary: The model-produced estimate for the treatment×time interaction effect at days 7 and 14. Interaction effect for follow-up visit time points day 100, 200 and 365 will also be assessed.

Intercurrent events: Death, AE/SAEs, rescue therapy outside of antibiotic use.

Strategy to handle intercurrent events: Treatment policy as primary estimand.

(3) Clinical endpoints including markers of general health, infective/microbiological and haematological outcomes across all time points measured, including admission to intensive care unit, survival, non-relapse mortality, relapse incidence; occurrence and severity of GvHD, overall and GvHD-free relapse-free survival and quality of life.

Population: As per primary estimand.

Variable(s): Overall and GvHD-free relapse-free survival.

Population-level summary: Log-rank test statistic, HR (with 95% CI).

Intercurrent events: Death unrelated to patient comorbidity (relapse-free survival only), death related to patient comorbidity (relapse-free survival only), loss to follow-up/patient withdrawal, AE/SAEs, rescue therapy outside of antibiotic use.

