### Analysis of primary estimand

The primary outcome of between-arm difference in alpha diversity change from baseline at day 28 (±3 days) will be analysed using a mixed-effects model, with change in alpha diversity from baseline as an outcome, with treatment arm, time, treatment-by-time interactions and stratification variables used in randomisation included as fixed effects and also a per-patient intercept included as a random effect. The subsequent model estimate for the treatment-by-time interaction term at day 28 will be the effect of interest as per primary estimand.

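### Treatment policy is declared for death, where no stool or questionnaire value can exist; the mixed model in effect estimates an undeclared effect, as if deaths before the time point had not occurred

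*Protocol article*

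**What the plan says.** Under Primary estimand, the intercurrent events are "Death, adverse/serious adverse events (AEs/SAEs), rescue therapy outside of antibiotic use, loss to follow-up/withdrawal". The strategy is "Treatment policy will be used to handle patient all defined intercurrent events", with the addition that "any patient response-assessment data collected postrandomisation will still be used in the analysis model if day 28 data is unavailable". The variable is "the change in alpha diversity (measured as inverse Simpson’s index) between IMT administration(at 14±3 days prior to HCT) and 28±3 days after HCT".

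Under Secondary estimands, item (1) covers EQ-5D-5L and QLQ-C30 scores at days 28, 100, 200 and 365. Item (2) covers the diversity measures and taxonomic composition at days 7 and 14 and again at days 100, 200 and 365. Both list death, and both give the strategy as "Treatment policy as primary estimand". Item (1) also lists loss to follow-up and withdrawal; item (2) does not.

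Under Analysis of primary estimand, the outcome "will be analysed using a mixed-effects model, with change in alpha diversity from baseline as an outcome". Arm, time, their interaction and the stratification variables are "included as fixed effects and also a per-patient intercept included as a random effect".

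One part of the article separates death from the other events. Under Secondary estimand (of primary outcome), treatment policy is kept for adverse events and rescue medication. Patients who die, withdraw or are lost are left out, under the name of a principal stratum strategy.

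**The concern.** The article's own account of treatment policy, under Overall approach, is that a patient is assessed by randomised arm whatever the event. That works when a value can still be measured afterwards, for example after an adverse event. It cannot work for death: there is no day-28 stool and no later questionnaire to use. The rule is therefore wrong as written for this event, not merely short on detail.

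The analysis does not stop at this gap. A likelihood-based mixed model keeps a deceased patient's earlier values and in effect continues that patient's course from them and from patients still observed. The estimate then answers a question that the estimand does not ask.

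The trial's rationale makes death unlikely to be ignorable. The Introduction reports that low diversity before transplantation goes with poor survival, and that survival was better with IMT in an earlier cohort. If deaths differ by arm, the effect had nobody died, the effect among survivors and an effect that counts death as a bad outcome can all differ. Readers of a day-365 quality-of-life result could take it as describing patients who were all alive.

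**Working it through.** **1. The plan's own figure.** Sample size and powering gives a difference of 3.46, an SD of 5.45, two-sided alpha of 20% and 80% power.
- n per arm = 2 × (1.2816 + 0.8416)² × (5.45 / 3.46)² = 2 × 4.508 × 2.481 = 22.4, rounded up to 23, so 46 in total.
- Noncentral-t power at 23 per arm is 80.3%.
- 46 / 0.92 = 50 recruited.

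The stated numbers reproduce. The dropout allowance is 0.08 × 50 = 4 patients without a day-28 value from any cause, death included.

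**2. Is the strategy definable for each event?**

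| Event | Does a value exist afterwards? | Treatment policy |
|---|---|---|
| Adverse event, rescue therapy | Yes, and it can be collected | Defined |
| Loss to follow-up, withdrawal | Yes, but unobserved | Defined; needs a missing-data assumption |
| Death | No | Undefined |

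**3. What the model targets.** The article gives no death rates, so the following is a large-sample illustration on assumptions.
- Visits at days 7, 14 and 28; SD 5.45; within-patient correlation 0.3 or 0.6.
- Day-28 mean changes of −4.70 (IMT) and −8.16 (placebo), as in the article, so the difference without deaths is 3.46.
- Assumed mean changes at days 7 and 14 of −4 and −5 (IMT) and −6 and −8 (placebo).
- Deaths between days 14 and 28, more likely when the day-14 value is low. Death thus depends on observed data only.
- A random-intercept model with arm-by-time effects, fitted to the observed values.

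| Deaths placebo / IMT | Correlation | Mixed model | Among those alive at day 28 |
|---|---|---|---|
| 4% / 4% | 0.3; 0.6 | 3.47; 3.46 | 3.47; 3.47 |
| 8% / 8% | 0.3; 0.6 | 3.48; 3.45 | 3.48; 3.45 |
| 12% / 4% | 0.3; 0.6 | 3.45; 3.48 | 3.29; 3.16 |
| 20% / 8% | 0.3; 0.6 | 3.46; 3.45 | 3.25; 3.02 |
| 30% / 15% | 0.3; 0.6 | 3.45; 3.47 | 3.19; 2.95 |

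In every row the model recovers the no-death contrast of 3.46 to within simulation error. The survivor contrast departs from it only when deaths differ by arm, by 3.46 − 3.29 = 0.17 to 3.46 − 2.95 = 0.51 units (5% to 15% of 3.46). The model is not malfunctioning: under these assumptions it estimates the hypothetical effect well. That effect is simply not the one declared.

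**4. Does another section repair this?** The complete-case estimand applies to the primary outcome only. Patients who happen to complete under their assigned arm are also not a principal stratum, which would consist of patients who would survive under either arm. Quality of life and late diversity have no alternative.

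**The case against.** The strongest reply has four parts.

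- **The protocol does separate death.** The secondary estimand of the primary outcome makes the right split between death and adverse events, and the article openly says which data enter the model. Both points stand, so it is unfair to say that death is never treated apart. But that estimand is secondary, covers one outcome and misnames its population.
- **The SAP will settle it.** The article defers to the SAP the estimands for the additional variables of secondary outcome 3. The strategies for the primary, quality-of-life and diversity estimands are fixed in the article itself, so restating them is a correction.
- **Loss to follow-up is not the same problem.** This stands. A reader might infer that treatment policy is equally impossible there. It is not: the value exists, and only an assumption about the missing data is needed.
- **Few patients should die by day 28, and no bias is shown.** This largely stands. A reader might infer that the model favours the arm with more deaths. The illustration does not support that: the model stayed at the no-death contrast, and it was the survivor contrast that moved. A reader might also want a fixed quality-of-life distortion at one year. That would need mortality rates and a score anchored at death, and the article gives neither. Equal means among survivors would not by themselves make the mixed model return zero, because it also uses the earlier scores of patients who later die.

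**Conclusion.** Wrong as written, and worth correcting. For death, the declared strategy cannot be carried out for day-28 diversity, for quality of life to day 365 or for the secondary diversity measures to day 365. The planned model in effect estimates a hypothetical effect, as if deaths before the time point had not occurred, under missing at random.

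At day 28 the practical effect is probably small if deaths are few or balanced: there was no material gap at equal rates of 4% or 8%, and gaps of 0.17 to 0.51 units appeared only under assumed unequal rates. At days 100 to 365 it may matter more. Without mortality rates in the article, neither size nor direction can be stated. The sample size is not called into question.

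**What to change.** - **All estimands:** limit treatment policy to adverse events and rescue therapy. It may also stay for loss to follow-up and withdrawal where these are listed, with the missing-data assumption stated.
- **Day-28 diversity:** state that the mixed model targets a hypothetical strategy for death. Add one composite sensitivity analysis that gives deaths before day 28 the worst outcome. A worst-rank analysis suits a change score: assigning the index's minimum of 1 would score each death as 1 minus baseline and so penalise patients with high baseline diversity most.
- **Quality of life and late diversity:** declare a while-alive strategy and report it beside survival by arm, or use a composite that includes death. The analysis must match the choice, since the random-intercept model would otherwise still extrapolate past death.
- **Secondary estimand of the primary outcome:** rename it a completer analysis.

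The cost is revised estimand wording and a few extra sensitivity tables. No new data are needed, the 50 patients stay, and the primary model need not change.

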##### Secondary estimand (of primary outcome)

A complete-case approach will be undertaken on the primary outcome(taking patients that provide primary outcome data across all response-assessment time points)

Population: As primary estimand.

Treatment: As primary estimand.

Variable: As primary estimand.

Population-level summary: As per primary estimand.

Intercurrent events: Death, AE/SAEs, rescue therapy outside of antibiotic use, loss to follow-up/withdrawal.

Strategy to handle intercurrent events: Treatment policy will be used in the event of AEs or rescue medication. In the event of death, withdrawal or loss to follow-up a principal stratum strategy is to be followed such that only those that complete the assessment period are to be included for analysis.

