### Analysis of secondary estimands

The complete-case analysis will follow the same model as defined in analysis of primary estimand (using only patients attending all visits as per estimand). Mixed-effect models incorporating a per-patient random effect alongside effects for time of assessment, and an interaction term of time-by-arm assessing changes in alpha diversity(inverse Simpson’s index, Chao-1, Shannon index, Faith’s PD) and β-diversity will provide treatment effects and 80% CIs at response assessments 1–5 and follow-up assessments 1–3 (see figure 1). Similar approaches will be used to assess changes in gut microbiome taxonomic composition based on shallow shotgun sequencing.

Overall survival (time from randomisation to death/date last seen alive) will be analysed using Kaplan-Meier methods and log-rank testing using the same stratification variables as per primary analysis model defined in analysis of primary estimand. Additional survival analysis will include non-relapse mortality and GvHD-free relapse-free survival.

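### The secondary estimand of the primary outcome is labelled a principal stratum but analyses observed completers, in an unchanged population and under three different inclusion wordings

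*Protocol article*

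**What the plan says.** All references are to the protocol article.

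- **Statistical analysis, Overall approach** commits the trial to the ICH E9(R1) estimand framework.
- **Primary estimand** defines the variable as the change in inverse Simpson's index from the time of IMT administration to day 28 (±3) after HCT. It uses treatment policy throughout and keeps whatever response-assessment data exist when the day-28 value is missing.
- **Secondary estimand (of primary outcome)** announces a complete-case approach, "taking patients that provide primary outcome data across all response-assessment time points". Population, treatment, variable and summary are all carried over from the primary estimand. Adverse events and rescue medication are handled by treatment policy. Patients who die, withdraw or are lost are handled differently: "a principal stratum strategy is to be followed such that only those that complete the assessment period are to be included for analysis".
- **Analysis of secondary estimands** applies the primary model again, "using only patients attending all visits as per estimand". The same paragraph lists response assessments 1 to 5 and follow-up assessments 1 to 3.

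**The concern.** In the framework that the protocol adopts, a principal stratum is defined by what would happen to a patient under both arms: here, those who would complete whether given IMT or placebo. The plan instead keeps those who did complete under the arm they were given. If treatment influences death, illness or withdrawal, completers on IMT and completers on placebo are different kinds of patient, and the comparison loses the protection of randomisation.

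The trial gives its own reason to expect such an influence. The Abstract hypothesises fewer complications and better HCT outcomes with IMT, and the Introduction reports improved overall survival in an earlier cohort given IMT before HCT.

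Two things are at stake. A completer comparison could be reported as a causal effect in a survivor-type stratum, and a difference from the primary result could be read as information about IMT when it reflects who was retained. Separately, the inclusion rule is open to more than one reading, so the analysis set could be chosen after the data are seen.

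**Working it through.** **1. Label against method.** The strategy attribute claims a principal stratum. The rule that implements it is observed completion. Using a principal stratum changes the target population, yet the population attribute is left as in the primary estimand, so both cannot hold. The article states no identifying assumption that would let observed completers stand in for the stratum.

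**2. When would the two coincide?** Only if treatment does not change who completes. An illustration on assumed values shows what happens otherwise. Take zero true effect, SD 5.45, a latent frailty correlated 0.3 to 0.7 with diversity change, and completion correlated 0.7 with the same frailty.

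| Completion, placebo → IMT (assumed) | Bias, correlation 0.3 | 0.5 | 0.7 |
|---|---|---|---|
| 80% → 80% | 0.0 | 0.0 | 0.0 |
| 80% → 90% | −0.18 | −0.29 | −0.41 |
| 70% → 85% | −0.26 | −0.42 | −0.59 |
| 60% → 80% | −0.34 | −0.56 | −0.78 |

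Where completion differs, the bias is about 0.2 to 0.8 units against IMT: 0.178/3.46 = 5% to 0.783/3.46 = 23% of the design difference.

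**3. The inclusion rule.** Three wordings appear:

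- data at every response-assessment time point;
- completion of the assessment period;
- attendance at all visits, which read literally could take in the three follow-up assessments out to day 365.

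Under the first and third, a patient who is alive, in follow-up and has both baseline and day-28 samples is excluded for one other missed sample or visit. A missed sample is not among the listed intercurrent events, and the variable needs only those two samples.

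**4. The plan's own sample size, reproduced.** Inputs from Sample size and powering: "two-sided alpha controlled at 20" per cent, "to have ≥80% power to detect a between-arm difference of 3.46 units", and "pooled SD of 5.45 estimated at day 28 post-HCT from mixed-effects model".

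- n per arm = 2 × (1.2816 + 0.8416)² × (5.45/3.46)² = 22.4, so 23.
- Exact noncentral-t power at 23 per arm is 80.3%.
- 46/0.92 = 50.

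This agrees with the stated 46 and 50.

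**5. How many completers?** The article gives no per-visit sample rate. On the stated dropout alone, 50 × 0.92 = 46. Otherwise assume five required samples, each missing with probability m. Independent misses give 50 × (1 − m)⁵. To allow for clustering within patients, the same rates are used with an assumed latent within-patient correlation.

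| m (assumed) | Independent | Correlation 0.5 | Correlation 0.8 |
|---|---|---|---|
| 5% | 50 × 0.774 = 38.7 | 41.7 | 44.2 |
| 10% | 50 × 0.590 = 29.5 | 35.4 | 39.5 |
| 15% | 50 × 0.444 = 22.2 | 30.1 | 35.4 |

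For the independent column, noncentral-t power for 3.46 at 19, 15 and 11 per arm is 74%, 67% and 57%. If all eight visits were required, independent misses would leave 50 × 0.95⁸ = 33 at 5% and 50 × 0.90⁸ = 22 at 10%.

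**The case against.** The strongest reply is that little is at stake. The section opens by calling this a complete-case approach, and the analysis section calls it that again, so a reader knows what will be done. Requiring complete data at every modelled time point is an ordinary meaning of complete case for a longitudinal model. The analysis is secondary, no power is claimed for it, and the primary model keeps partial data.

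Much of this stands. It limits the consequence, and it means the power figures above describe loss of precision, not a broken promise. It does not rescue the label: the strategy attribute still names a principal stratum, and the population attribute still contradicts it. Nor does it settle which of the three inclusion wordings applies.

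Three stronger readings are tempting, and the document does not support them.

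- **That the completer set will be much smaller.** This depends wholly on an assumed rate, on independence and on five stool samples. The visit schedule is in a figure and appendices that are not shown. The illnesses that would cause missed samples also suggest clustering, which reduces the loss.
- **That this is the only check on the primary result.** The article defers full methods to a SAP that is not shown and may contain others.
- **That the plan is deficient for lacking a tipping-point or survivor-effect analysis.** Those are matters commonly left to the SAP, and their absence from a condensed article is not a fault.

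**Conclusion.** The point holds as an error in how this secondary estimand is specified. The named strategy, the stated population and the analysis set do not agree, and the inclusion rule is both inconsistent and stricter than the variable requires. Followed as written, the trial would present a comparison selected after randomisation as a principal-stratum effect.

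The bias is zero in the illustration when completion is equal between arms, and about 0.2 to 0.8 units against IMT in the unequal scenarios assumed. The loss of patients is unknown: 46 of 50 remain on the stated dropout alone, and about 39 down to 22 under 5% to 15% independent missingness at five assumed samples, with more retained under clustering. The primary analysis and the sample size of 46 evaluable and 50 recruited are unaffected.

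**What to change.** 1. In Secondary estimand (of primary outcome), remove the principal-stratum strategy. Describe the analysis as a complete-case sensitivity analysis of the primary estimand, and state that it carries no causal survivor or completer interpretation. The carried-over population attribute then no longer conflicts with the strategy.
2. Use one inclusion rule there and in Analysis of secondary estimands: patients with a baseline sample and a day-28 (±3) sample.
3. Settle both changes before unblinding.

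If a true principal stratum is wanted, the alternative is to define it by completion under either arm, change the population attribute to match, and state the identifying assumptions.

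The cost is a few lines of wording in the protocol and the matching SAP text. No new data are needed, and neither the sample size nor the primary model changes.
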